# **10. Handling of adverse events**

## **10-1. Response to patients when adverse events occur**

When adverse events are observed, the principal investigator or sub-investigator should promptly take appropriate measures and describe them in the medical records and eCRF without any discrepancy.

## **10-2. Reports on outbreaks of diseases**

When the following diseases (adverse events for which a causal relationship to the test drug or test procedure cannot be denied) occur and the principal investigator recognizes them, the principal investigator reports the fact to the manager of the participating medical organization and the accredited Clinical Research and Review Board and the Ministry of Health, Labour, and Welfare/PMDA within each period, as well as to the Clinical Research and Monitoring Committee of Tokyo Medical and Dental University:

| Unknown and known | Symptoms and conditions | Deadline for reporting |
| --- | --- | --- |
| Unknown | ・Death | 7 days |
|  | ・Diseases that may lead to death, etc. |  |
| Known | ・Death | 15 days |
|  | ・Diseases that may lead to death, etc. |  |
| Unknown | ① Inpatient hospitalization or prolongation of existing hospitalization  ② Disability  ③ Diseases that may lead to disability, etc.  ④ Diseases, etc. that are serious following the above and diseases that may lead to death or death  ⑤ Any congenital disease or anomaly in the offspring of a treated patient. |  |
| Other than the above (e.g., abnormal values, mild symptoms of disease, etc., mild but frequent, including bias in occurrence due to facilities) | | Periodic Report |

- The occurrence of diseases and their progress thereafter should be reported during periodic reporting.

# **11. Handling of the occurrence of non-compliance with the research protocol**

　The investigator shall promptly report to the manager of the medical institution when the clinical research is not in compliance with the Ministerial Authority or research protocol. (Report to the principal investigator, if known by the research sub-investigator) In the event of significant noncompliance, immediately hear the opinion of the accreditation committee. Nonconformance (Unified Form 7) will be reported periodically (Unified Form 5). In addition, the principal investigator will report to the manager of the participating medical organization and inform the research-representative physician. In case of significant noncompliance, the research representative physician should promptly seek the opinion of the accreditation committee. (Unified Form 7) Provide information to other investigators as soon as they know that the multicenter study is incompatible. Noncompliance should be reported in periodic reports (Unified Form 5).

# **12. Reporting and methods to administrators of medical institutions**

　The principal investigator will report the following items in writing to the manager of the medical institution (hospital director).

- The investigator shall promptly report to the manager of the participating medical organization if he/she knows that the clinical research is not in compliance with this Ministerial Authority or the research protocol (hereafter referred to as "incompatibility") (uniform forms 5 and 7).
- Principal investigator, research sub-investigator, and statistician.
- Persons who are listed in the study protocol and report to the manager about donations, manuscript writing, lectures, and other involvement in the work of the drug, marketed by the marketing author, used in the clinical study (Forms A-E).
- Promptly report to the manager if there is an opinion from the certified review board (uniform forms 4 and 13)
- Information provided to the principal investigator by the representative investigator in the multicenter study was promptly reported to managers.
- The primary endpoint report or clinical study report and summary will be submitted to the manager of the participating medical organization without delay when prepared or published (such a report).
- When the principal investigator (representative physician) submits the plan, the relevant information is reported to the manager for approval. (Initial application)
- Reports in case of illness within the prescribed period (Forms 8, 9, and 10; Form 2-1, 2-2; Form 6 for periodic illness reports; Form 3 for regular illness reports)
- A report to the manager within 30 days when a failure may occur and that disease, etc. (similar to serious adverse events) may occur (uniform forms 5 and 7).

# **13. Study completion, discontinuation, or interruption**

## **13-1. Completion of the study**

Upon completion, discontinuation, or interruption of the study at each institution, the principal investigator will submit the study completion, discontinuation, or interruption report to the head of the research institution ( head of the hospital) through the Clinical Trials Management Center. When the study is conducted in a multicenter setting, completion, discontinuation, or interruption reports will also be submitted to the representative study physician. In hospitals, the report shall be completed, discontinued, or interrupted, based on the report at the time of the implementation status survey at the end of each fiscal year.

After completion, discontinuation, or interruption is reported, the status is registered with the jRCT registry.

## **13-2. Discontinuation or interruption of research**

・ The principal investigator will consider whether or not to continue the study if any of the following is applicable.

1) When significant information on the quality, safety, and efficacy of the test drug is obtained.

2) When it is judged that it is difficult to recruit the study participants and to achieve the planned cases.

3) When the Certified Review Board determines that it is difficult to accept an order for a change in the implementation plan, etc.

If the Certified Review Board recommends or directs discontinuation, the study should be discontinued.

When the study is conducted at multiple institutions, the above items should be reviewed by the research representative physician or committee specified in the research protocol, and whether to continue the study should be considered.

・ If a decision is made to terminate or suspend a study, it should be promptly reported in writing to the head of the research institution (the head of the hospital) together with the clinical research review board. The head of the research institution (the head of the hospital) shall report to the Ministry of Health, Labour, and Welfare if the degree of non-compliance with the Medical Research Guidelines is discontinued due to its severity.

# **14. Statistical matter**

Details of statistical analyses will be specified in a separate statistical analysis plan.

## **14-1. Full analysis set**

　　The definitions of the analyzed population are as follows:

　Intention-to-treat (ITT) Group

All randomized populations will be included.

・Modified intention-to-treat (mITT) group

Patients in the ITT population excluded: ① patients who had never received a treatment either aspirin or placebo; ② patients who did not have any post-randomization data; and ③ patients who met the well-defined and objectively determinable criteria for selection and exclusion.

・Safety analysis set (Safety Analysis Set; SAS)

The study population will be randomized and will receive the treatment (aspirin or placebo).

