## **4-2. Exclusion criteria**

**Exclude patients who meet any of the following criteria**

1) Individuals without independent premorbid activities of daily living (pre-stroke mRS ≧4).

2) Patients with dissecting cerebral aneurysms in whom parent artery occlusion was attempted

3) Patients with recurrent ruptured cerebral aneurysms after cerebral aneurysm coil embolization

4) Patients with cerebral arteriovenous malformations, moyamoya disease, and other cerebral aneurysms or ruptured infectious cerebral aneurysms

5) Patients treated simultaneously for two or more aneurysms

6) Patients already taking antiplatelet drugs

7) Patients with a history of allergy to lactose, aspirin, or salicylic acid preparations

8) Patients who cannot undergo MRI

9) Patients with contraindications to aspirin

10) Other patients considered by the treating physician not appropriate to participate in the study

[Rationale Setting] 1), 2), 3), 4), 5), 6) Effect on Evaluation of Efficacy

　　　　　　　　 　7), 8), 9), 10) For safety considerations

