## 9-2. Discontinuation during the period from embolization to 3 months after surgery

Discontinuation criteria

1) When a participant has offered to decline research participation or withdrawn consent

2) When it is found that the eligibility is not satisfied after registration

3) When the entire study is discontinued

4) When the physician considers it appropriate to discontinue the study for other reasons

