## **14-3. Statistical analysis**

**Analysis of the primary endpoint**

1) Incidence of intraoperative thrombotic complications

2) Incidence of symptomatic ischemic involvement in MRI-DWI (IRC).

The superiority of the aspirin-treated group to the placebo-treated group will be tested in mITT using Cochran-Mantel-Haenszel (CMH test stratified by age (≧65 years, <65 years), sex (men, women), WFNS grade (I-III, IV-V), and modified Fisher grade (0-2, 3-4. Considering the multiplicity of tests, the two-sided significance level in the comparison between the groups for each endpoint was 2.5 %. The number and percentage of patients with events were calculated for each group, and the difference in the percentages between the two groups (aspirin group vs. placebo group) was calculated with a 97.5% confidence interval.

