**Analysis of the key secondary endpoints**

1) Incidence of all bleeding events within 14 days of onset

2) Incidence of global cerebral ischemic events in the first 14 days after MRI radiography after surgery

For mITT, the number and percentage of patients with events will be calculated in each group, and the difference in the percentage between the two groups (aspirin-placebo group) and the 95% confidence interval will be calculated. If the upper limit of the confidence interval was less than 10%, non-inferiority was demonstrated. Comparisons between the groups for each endpoint will be based on the closed test procedure described above.

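### Item ③ of the mITT definition is inverted as written and, even read as excluding ineligible patients, is not limited to facts fixed before randomisation

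*Protocol*

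**What the plan says.** Protocol section 14-1 defines three sets. For the ITT set, "All randomized populations will be included". The mITT takes out of it patients who never received study treatment (①), patients with no post-randomisation data (②), and "patients who met the well-defined and objectively determinable criteria for selection and exclusion" (③). The Safety Analysis Set holds randomised patients who received treatment.

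Section 14-3 then allocates the sets:

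- Primary endpoints: "The superiority of the aspirin-treated group to the placebo-treated group will be tested in mITT using Cochran-Mantel-Haenszel", at a two-sided 2.5% level for each endpoint.
- Key secondary endpoints (bleeding and cerebral ischaemic events): "For mITT, the number and percentage of patients with events will be calculated in each group". The criterion is "If the upper limit of the confidence interval was less than 10%, non-inferiority was demonstrated".
- Other secondary and exploratory endpoints: also the mITT.
- Adverse event and adverse reaction rates: the Safety Analysis Set.
- The ITT set: no analysis.

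Section 9-2 lists, among the reasons for discontinuation between embolization and 3 months, "When it is found that the eligibility is not satisfied after registration".

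**The concern.** The sentence that fixes the confirmatory population does not say what it must mean. A patient who meets the selection criteria is an eligible patient, so item ③ as printed removes the people the trial was designed to study.

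The likely intention is to remove patients who violated eligibility. Leaving such patients out can be defended when the violation rests on facts fixed before randomisation, because treatment cannot then have influenced it. Item ③ has no such limit. If a patient can be declared ineligible on something that happened or was learned after dosing, the removal may be related to treatment or outcome, and the comparison is no longer protected by randomisation. Both superiority tests and the bleeding non-inferiority comparison depend on this set, and the protocol names no analysis of all randomised patients to set beside them.

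**Working it through.** **1. The plan's own figure.** Section 14-2 assumes 15% against 5%, two-sided alpha 0.025 and 90% power, and states 230 per group. Exact enumeration of a two-sided Fisher test at 230 per group gives power 90.2%, so 460 is reproduced on that basis. For dropout, 460 / 0.95 = 484.2, against 484 stated. The allowance is 484 − 460 = 24 patients, 12 per group. The sample size does not depend on item ③.

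**2. The literal reading.** Item ③ stands in a list of those taken out of the ITT population. Its verb is *met* and its object covers both selection and exclusion criteria. Reading it as *met an exclusion criterion* deals with one half of the object but not the other. Applied as printed, it leaves no correctly enrolled patient in the mITT.

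**3. The probable reading, set against the timing of events.**

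| Step | Where | Timing |
| --- | --- | --- |
| Eligibility entered, drug number issued | 6-4 | before dosing |
| Single dose by gastric tube | 6, 6-3 | after induction, before embolization |
| Exclusion 2 (parent artery occlusion attempted in a dissecting aneurysm) | 4-2 | can be settled during the procedure |
| Exclusion 5 (two or more aneurysms treated together) | 4-2 | can be settled during the procedure |
| Ineligibility as a discontinuation reason | 9-2 | embolization to 3 months |

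Two listed exclusions can therefore become true after dosing, and the protocol itself expects some ineligibility to be found after embolization. Since treatment is one dose already given, what remains to discontinue at that stage is follow-up.

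**4. How few patients matter.** All event counts here are assumed. The documents give no expected bleeding rate.

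*Bleeding non-inferiority, margin 10 points.* Let d = p₁ − p₂. The Wald upper limit is d + 1.96·√[p₁(1−p₁)/n₁ + p₂(1−p₂)/n₂]. The Newcombe upper limit is d + √[(u₁−p₁)² + (p₂−l₂)²], where u₁ and l₂ are Wilson limits. For 26/230 against 11/230, d = 11.30 − 4.78 = 6.52 points and SE = 2.518, so the Wald limit is 6.52 + 1.96 × 2.518 = 11.46.

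| Bleeders removed | Aspirin | Placebo | Wald / Newcombe upper limit | Below 10? |
| --- | --- | --- | --- | --- |
| None | 26/230 | 11/230 | 11.46 / 11.71 | no |
| 3 aspirin only | 23/227 | 11/230 | 10.15 / 10.41 | no |
| 4 aspirin only | 22/226 | 11/230 | 9.70 / 9.97 | yes |
| 5 aspirin only | 21/225 | 11/230 | 9.25 / 9.52 | yes |
| About 19% of each arm | 21/225 | 9/228 | 9.95 / 10.27 | depends on method |
| 5 from each arm | 21/225 | 6/225 | 11.01 / 11.40 | no |

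*A primary endpoint, alpha 0.025, unstratified pooled z-test.* Here z = |p₁ − p₂| / √[p̄(1−p̄)(1/n₁ + 1/n₂)].

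- Aspirin 20/230 against placebo 35/230: p̄ = 55/460 = 0.1196, SE = 0.0303, z = 2.156, p = 0.031.
- One aspirin event removed (19/229 against 35/230): z = 2.301, p = 0.021, so the result becomes significant.
- One event removed from each arm (19/229 against 34/229): z = 2.191, p = 0.028, so it does not.

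A handful of exclusions can change a borderline result when they fall in one arm. When they fall evenly, the examples mostly do not change.

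**The case against.** The inversion is a slip of language. Nobody could apply the literal text, other sentences in section 14-1 are also in broken English, and one word repairs it. That is fair, but no other place in the protocol states the intended rule, so the printed sentence governs. The repair also leaves the missing time limit untouched.

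The protocol contains real safeguards. Criteria must be objectively determinable (14-1). Eligibility is entered before a drug number is issued, and each participant's inclusion or exclusion is to be fixed before unblinding (6-4). Section 9 requires examinations at discontinuation to evaluate efficacy and safety. These stand, and they make removal from one arm only unlikely. They are incomplete for two reasons. The emergency key may be opened for intraoperative thrombus, which is primary endpoint 1. And an assessor blind to arm may still know the outcome: if aspirin changes the outcome, outcome-related removal differs by arm even under blinding.

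A reader might infer that a patient too unstable for the 6–48 h scan could be ruled out under "Patients who cannot undergo MRI". The text does not support this well. Section 4-2 gives safety as the rationale for that criterion, which fits a contraindication known at screening. No section says that a missed scan makes a patient ineligible in retrospect; that is missing outcome data. Exclusions 2 and 5 are not themselves bleeding or ischaemic events.

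Serious bleeds in dosed patients are in any case recorded as adverse events (7-2) and tabulated in the Safety Analysis Set, though not tested there against the margin. An ITT sensitivity analysis may also stand in the separate statistical analysis plan, which is not at hand.

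**Conclusion.** The point holds as a defect in the rule that defines the confirmatory population. That item ③ is inverted, that it carries no time limit and that section 14-3 gives the ITT set no role can all be read directly from the protocol. That it was meant to say *violated* is an inference, though a safe one.

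It would be tempting to conclude that patients harmed by aspirin will be removed and non-inferiority on bleeding falsely claimed. The documents do not show this. The change from fail to pass needs assumed counts and removal from the aspirin arm alone, which blind fixing of exclusions works against. Under equal removal the test still fails, and under proportional removal it straddles the margin. The calculations show only that a borderline result is sensitive to a few exclusions, well within the 12 per group allowed for dropout. They rest on unstratified methods and do not predict the trial's result.

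Item ② needs no change: a dosed patient has intraoperative data, so it removes almost nobody beyond item ①.

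**What to change.** - **Section 14-1:** delete item ③, or restate it as violation of listed eligibility criteria that can be proved from data dated before randomisation, judged by people blind to both arm and outcome.
- **Section 14-3, primary endpoints:** repeat both tests in the ITT set already defined.
- **Section 14-3, key secondary endpoints:** run the bleeding non-inferiority comparison also in the Safety Analysis Set.
- **Section 9-2:** state that outcome data continue to be collected for dosed patients found ineligible, unless consent is withdrawn.

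The cost is an amendment to the wording (and to the statistical analysis plan where it repeats the definition), a little more follow-up and analysis, and slight dilution of the effect by a few ineligible patients. The sample size is unchanged.

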## **14-2. Number of patients planned and rationale**

Target sample size 484

The rationale for setting the target number of patients :

The primary endpoints of this study were the rates of intraoperative thrombotic morbidity and symptomatic ischemic pathology on MRI-DWI (IRC). Rie et al reported^12^ a total of 8.8% incidence of thromboembolism in 159 patients with cerebral aneurysms who received intraoperative antiplatelet therapy and 17.6% in 102 patients who did not. In addition, at our institution and relevant institutions, based on the imaging findings obtained on MRI DWI on the day after the operation, in 27 patients who underwent endovascular aneurysm embolization for cerebral aneurysms, 14.8% (4 of 27 patients) showed ischemic lesion 15 mm or higher.

Therefore, the incidence of intraoperative thrombotic complications in the placebo-treated group and the incidence of symptomatic ischemic disease on MRI-DWI were assumed to be 15%. Assuming that aspirin treatment improves both by 10%, we assumed that the incidence of intraoperative thrombotic morbidity in the aspirin group and the incidence of symptomatic ischemic pathology on MRI-DWI would be 5% each. Under these assumptions, a two-sided significance level of 2.5% would result in a sample size of 460 patients (230 patients in each group), requiring 90% power for each intergroup comparison of the endpoints. The target sample size was 484 patients (242 in each group) with a dropout rate of approximately 5%.

## **14-3. Statistical analysis**

**Analysis of the primary endpoint**

1) Incidence of intraoperative thrombotic complications

2) Incidence of symptomatic ischemic involvement in MRI-DWI (IRC).

The superiority of the aspirin-treated group to the placebo-treated group will be tested in mITT using Cochran-Mantel-Haenszel (CMH test stratified by age (≧65 years, <65 years), sex (men, women), WFNS grade (I-III, IV-V), and modified Fisher grade (0-2, 3-4. Considering the multiplicity of tests, the two-sided significance level in the comparison between the groups for each endpoint was 2.5 %. The number and percentage of patients with events were calculated for each group, and the difference in the percentages between the two groups (aspirin group vs. placebo group) was calculated with a 97.5% confidence interval.

**Analysis of the key secondary endpoints**

1) Incidence of all bleeding events within 14 days of onset

2) Incidence of global cerebral ischemic events in the first 14 days after MRI radiography after surgery

For mITT, the number and percentage of patients with events will be calculated in each group, and the difference in the percentage between the two groups (aspirin-placebo group) and the 95% confidence interval will be calculated. If the upper limit of the confidence interval was less than 10%, non-inferiority was demonstrated. Comparisons between the groups for each endpoint will be based on the closed test procedure described above.

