# **<Overview>**

| **Study title** | Pre-surgical Aspirin Administration for the Prevention of Thromboembolic Complications of Coil Embolization for Ruptured Aneurysms  (ASTOP study) |
| --- | --- |
| **Purpose of the study** | During endovascular treatment of ruptured cerebral aneurysms, thromboembolisms are known as uncontrollable therapeutic complications, and further improvement of treatment outcomes can be expected by controlling these complications. We hypothesized that the administration of preoperative antiplatelet agents for endovascular treatment may reduce thromboembolic complications.  The patients who are planned to undergo endovascular treatment for acute ruptured saccular cerebral aneurysms will be randomly assigned to receive aspirin or placebo preoperatively. The incident rate of intraoperative thromboembolic events, postoperative new neurological dysfunction, new cerebral infarction in postoperative magnetic resonance imaging (MRI), perioperative cerebral ischemic events or all hemorrhagic events, and mRS at 3 months will be compared between the two groups. |
| **Study Design** | A multicenter, randomized, double-blind, placebo-controlled study |
| **Phase** | Confirmatory study |
| **Test drug** | Generic name: Aspirin  Dosage form: Powder  Storage conditions: Storage at room temperature |
| **Inclusion criteria** | Patients who meet all of the following criteria   1. Patients with ruptured cerebral aneurysms in the acute phase 2. Patients scheduled for aneurysm embolization within 72 h of onset 3. Patients aged 20 years or older at the time of presentation 4. Patients for whom written informed consent has been obtained from the person or their legally acceptable representative (e.g., spouse, parent, adult child) for participation in the study. |

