# **2.** **Purpose of the study**

　During EVT of ruptured cerebral aneurysms, thromboembolic complications are known to be uncontrollable therapeutic complications and further improvement in treatment outcomes can be achieved by controlling these complications. We hypothesized that the administration of preoperative antiplatelet agents for EVT may control thromboembolic complications.

　For embolization of acutely ruptured saccular cerebral aneurysms, patients will be randomized to receive aspirin or placebo preoperatively to test for differences in the incidence rate of intraoperative thromboembolic events, new postoperative neurological dysfunctions, new cerebral infarctions on postoperative MRI, perioperative cerebral ischemic events, any hemorrhagic events, and 3-month mRS between the two groups.

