# **7.** **Endpoint**

## **7-1.** **Items related to the evaluation of efficacy**

　Primary outcomes

1) Incidence rate of intraoperative thrombotic complications

It is defined as the proportion of patients with evidence of cerebral angiographically evident thrombus formation in the vicinity of the aneurysm neck or parent artery during surgery.

2) Incidence rate of symptomatic ischemic lesions on MRI diffusion-weighted imaging (DWI) evaluated by the Independent Review Committee (IRC)

It is defined as the percentage of patients with acute-phase ischemic lesions on MRI-DWI performed 6–48 h postoperatively and with concordant neurologic findings.

Key secondary outcomes

1) Incidence rate of all bleeding events within 14 days of enrollment

As a basic protocol, a head CT is performed within 48 h postoperatively and at 14±2 days postoperatively. Additionally, imaging evaluations were conducted as required. The incidence rate of all bleeding events is defined as the percentage of patients with a ruptured aneurysm (symptomatic subarachnoid or intracerebral hemorrhage due to rupture of an aneurysm of interest), a hemorrhagic stroke (symptomatic subarachnoid and intracerebral hemorrhage not due to rupture of target aneurysm, or the proportion of patients who experienced "major hemorrhage" according to ISTH criteria within 14 days post-registration.

2) Incidence rate of cerebral ischemic events in the first 14 days after MRI

The basic protocol is head CT performed within 6–48 h after surgery and 14 ± 2 days after surgery. This is defined as the percentage of patients with transient ischemic attack within 14 ± 2 days after MRI (neurological symptoms lasting less than 24 h with or without imaging findings) or ischemic stroke (focal neurological symptoms lasting more than 24 h and ischemic lesions confirmed by head CT or MRI) during the study period.

Other secondary outcomes

1) Incidence rate of symptomatic ischemic lesions in MRI-DWI evaluated by INV.

2) mRS at 3 months

Assessment is based on mRS scoring 3 months after the onset of subarachnoid hemorrhage.

　Exploratory outcomes

1) Ischemic lesions on MRI-DWI (number and size: 0–4 mm, 5–9 mm, 10–14 mm, 15 mm or greater, categorized as IRC or INV)

2) Incidence rate of cerebral hemorrhage along the tube tract for ventricular drainage on CT scans in the first 14 days after EVT.

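### Post-MRI cerebral ischemic events are judged only by non-inferiority to placebo with an unexplained 10-point margin, so the pre-specified verdict cannot show a benefit of aspirin

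*Protocol*

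**What the plan says.** Protocol section 14-3, under the analysis of the key secondary endpoints, names two outcomes: all bleeding events and "Incidence of global cerebral ischemic events in the first 14 days after MRI radiography after surgery". For both, "the difference in the percentage between the two groups (aspirin-placebo group) and the 95% confidence interval will be calculated". One decision rule then covers both: "If the upper limit of the confidence interval was less than 10%, non-inferiority was demonstrated". The paragraph closes with "Comparisons between the groups for each endpoint will be based on the closed test procedure described above", but the text above it describes no closed procedure. It contains only the 2.5% significance level applied to each of the two primary endpoints.

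The surrounding sections point towards showing a reduction:

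- The Overview describes "A multicenter, randomized, double-blind, placebo-controlled study", so the comparator is inactive.
- Section 2 states: "We hypothesized that the administration of preoperative antiplatelet agents for EVT may control thromboembolic complications". It then lists perioperative cerebral ischemic events among the outcomes to be examined for differences between the groups.
- For the primary endpoints, section 14-3 says: "The superiority of the aspirin-treated group to the placebo-treated group will be tested in mITT". The investigator-assessed DWI outcome and the 3-month mRS are also compared with CMH tests.
- Section 7-1 places the post-MRI ischemic endpoint under "Items related to the evaluation of efficacy".

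**The concern.** Against an active control, non-inferiority can show that a known effect is preserved. Against placebo it shows only that the drug is not worse by more than the margin. For bleeding, where aspirin may do harm, that is a sensible question. For ischemic events, where the stated expectation is fewer thromboembolic complications, the verdict carries no information about benefit.

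The margin adds to the difficulty. Section 14-2 assumes that aspirin lowers each primary endpoint from 15% to 5%, a gain of 10 points. The ischemic rule declares success when an excess of 10 points has been excluded, so the tolerated excess is as large as the whole benefit hoped for on the primaries. No reason for that size is given.

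What is at stake is the meaning of a key secondary result. The rule can be reported as met when aspirin does nothing, or when slightly more ischemic events occurred on aspirin.

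**Working it through.** **1. The plan's own figure.** Section 14-2 gives 15% versus 5%, two-sided 2.5%, 90% power and 230 per arm. The pooled normal formula gives 222 per arm, or 241 with continuity correction. Exact power of Fisher's test first reaches 90% at 229 per arm and is 90.2% at 230. The figure is therefore reproduced, and 230 × 1.05 = 241.5 gives the 242 enrolled per arm. It concerns the primary endpoints only. No rate or power is stated for the non-inferiority test.

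**2. Inputs for the rule.** n = 230 per arm; margin 0.10; two-sided 95% interval for aspirin minus placebo. The protocol does not name the interval method, so a Wald interval is assumed. The placebo rate p is also an assumption, ranged from 5% to 40%; 15% is the rate used for the primaries.

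Success means: (pA − pP) + 1.96 × √[pA(1 − pA)/230 + pP(1 − pP)/230] < 0.10, with observed proportions.

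**3. A drug with no effect.** Approximately, P(success) = Φ(0.10/SE − 1.96), with SE = √[2p(1 − p)/230]. At p = 15%, SE = √(2 × 0.15 × 0.85/230) = 0.0333, and Φ(3.003 − 1.96) = Φ(1.043) = 85.2%. Exact binomial enumeration also gives 85.2%.

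**4. Probability of meeting the rule, exact enumeration, 230 per arm.**

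| Assumed placebo rate | No true difference | Aspirin 3 points worse | Aspirin 5 points worse |
|---|---|---|---|
| 5% | 99.8% | 86% | 54% |
| 10% | 94.5% | 65% | 37% |
| 15% | 85.2% | 53% | 30% |
| 20% | 76.7% | 45% | 25% |
| 30% | 64.8% | 37% | 21% |
| 40% | 59.4% | 34% | 20% |

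**5. A worked outcome.** With 41/230 on aspirin (17.8%) and 34/230 on placebo (14.8%), the difference is +3.0 points. SE = √(0.1783 × 0.8217/230 + 0.1478 × 0.8522/230) = 0.0344, so the upper limit is 3.0 + 1.96 × 3.44 = 9.8 points. The rule is met with more ischemia on aspirin.

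**6. A superiority criterion on the same data.** If the upper limit must lie below 0, a drug with no effect succeeds about 2.4% to 2.6% of the time over the same range of rates. Power at two-sided 5% is Φ{[d√n − 1.96√(2p̄(1 − p̄))] / √[p1(1 − p1) + p2(1 − p2)]}, where d = p1 − p2 and p̄ is their mean:

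- 15% vs 5%: (1.517 − 0.832)/0.418 = 1.64, power 95%.
- 15% vs 10%: (0.758 − 0.917)/0.466 = −0.34, power 37%.
- 20% vs 10%: 85%. 20% vs 15%: 29%.

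**The case against.** Five arguments limit the point.

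- **The efficacy heading settles little.** Bleeding is listed under the same heading in section 7-1, and non-inferiority is acceptable there. The case has to rest on section 2 and on the placebo comparator. Even section 2 puts hemorrhagic events in the same list of differences, so its weight comes from the hypothesis that aspirin controls thromboembolic complications.
- **The window is late.** The endpoint counts events in the 14 days after the MRI, following a single preoperative dose. Its definition does not exclude vasospasm, and the 14-day form in section 8 records infarction due to vasospasm. A no-excess-harm question is therefore possible. The protocol does not state that purpose, and it would still need a reasoned margin.
- **A high pass rate at no difference is simply the power of a non-inferiority test.** This is true. The figures in the second column become a problem only because the question asked elsewhere is about benefit.
- **The difference and its 95% interval are reported anyway.** This stands: an upper limit below 0 would be informative. A reader might infer that the endpoint tells us nothing about prevention of ischemia. That is too strong; the limitation applies to the non-inferiority verdict.
- **The statistical analysis plan may add detail.** It may, but the protocol already fixes the rule and the margin, so a different criterion there would conflict with it.

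A reader might also infer that any inert or moderately harmful drug passes. The figures do not support that: at placebo rates of 10% to 20%, a drug truly 5 points worse passes only 37% to 25% of the time. Nor does the protocol say that it would present non-inferiority as evidence of efficacy.

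**Conclusion.** The point holds in a limited form. The only pre-specified criterion for post-MRI ischemic events is non-inferiority to placebo with an unexplained margin, and it does not answer the question about differences posed in section 2. A drug with no effect meets it with probability 99.8% to 59% over assumed placebo rates of 5% to 40%; a drug truly 3 points worse does so with probability 86% to 34%. These figures rest on 230 evaluable patients per arm, a Wald interval and the assumed rates. With 242 per arm the no-effect figure at 15% is 86.9% instead of 85.2%.

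It would go too far to infer that the trial's main conclusions are compromised. Both primary endpoints are tested for superiority, the sample size reproduces, and data collection is untouched. This should be fixed, but it concerns one key secondary endpoint and is not a flaw in the design as a whole.

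**What to change.** Before unblinding, amend section 14-3 as follows, and carry the change into the analysis plan.

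- Confine the 10-point non-inferiority rule, as a success criterion, to bleeding.
- For ischemic events, pre-specify a superiority test: the CMH test stratified as for the primaries, at two-sided 5%, with an upper 95% limit below 0 as the criterion on the difference. State which governs should the two disagree.
- Write out the testing order that the reference to a closed procedure presupposes, and give this endpoint its place in it.
- If a no-excess-harm check on ischemia is also wanted, keep it as a first step with a justified margin and follow it with superiority. An upper limit below 0 is also below any positive margin, so the fixed sequence costs no alpha.
- State that non-inferiority on this endpoint is not evidence of efficacy.

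The cost is wording only: no new patients and no new data. The sponsor gives up an easily met claim. Superiority power is also modest for effects smaller than those assumed for the primaries: about 37% for 15% versus 10%, against about 95% for 15% versus 5%. The 10-point effect behind the higher figure is assumed in section 14-2 for the primary endpoints only.
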